**Methods:**

The Alcohol & Metabolic Comorbidities in PLWH: Evidence Driven Interventions Study (ALIVE-Ex Study, NCT03299205) is a longitudinal, prospective, interventional study to determine the effects of an aerobic exercise protocol on improving dysglycemia among PLWH with at-risk alcohol use. The intervention is a moderate intensity aerobic exercise protocol implemented 3 days per week for 10 weeks at the Louisiana State University Health Sciences Center-New Orleans. Participants who have a fasting blood glucose level between 94 and 125 mg/dl will be enrolled in the study. Oral glucose tolerance tests, fitness assessments, and skeletal muscle biopsies will be performed pre- and post-exercise intervention. The primary outcome is to determine whether the exercise protocol improves measures of whole-body glucose-insulin dynamics, cardiorespiratory fitness, and skeletal muscle metabolic and bioenergetic function. Secondary outcomes are to determine whether the exercise intervention improves cognitive function and overall quality of life. Results generated will demonstrate the effect of exercise on glycemic measures in PLWH with subclinical dysglycemia and at-risk alcohol use.

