### Screening

After informed consent, participants are instructed to fast and not drink alcohol overnight. Participants are considered eligible if they have a fasting blood glucose of 95–124 mg/dL, measured by a single-use auto-disabling finger stick device and glucose meter (True Metrix® Pro Blood Glucose Monitoring System, McKesson).

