### Oral glucose tolerance test (OGTT)

Blood is collected at time 0, after which participants ingest a calibrated dose (10 oz) of a glucose solution (Trutol; 75 g glucose) over a 5-to-15-min period. Blood is collected at 1 and 2 h following the glucose drink. During that time, participants are seated without eating, drinking, or smoking and complete the following questionnaires: demographics, AUDIT, and TLFB. At the end of the OGTT, participants are monitored for signs of hypoglycemia. OGTTs are performed at two timepoints, the first one at least a week before the first exercise session and the second 3 days after the last exercise session.

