### Muscle biopsy

Participants are instructed to fast for 9 h prior to the biopsy visit. TLFB, blood pressure, weight, and waist and hip circumference are collected. Following the 0 h blood collection, participants consume a defined (calorie and nutrient composition) meal (i.e., Ensure, Carnation Instant Breakfast). Ninety (90) minutes later, a skeletal muscle biopsy is performed under ultrasound guidance by interventional radiologists associated with LSUHSC-NO. Using sterile technique, 2 cc of 2% lidocaine is injected at the incision site on the right vastus lateralis muscle. A 14-gauge core needle is inserted through a single-entry point. Samples of the vastus lateralis are obtained on 6 passes. Pressure is held on the biopsy site for 5 min, followed by pressure dressing for 1 h. After that time, the dressing is removed. Participants are contacted 24 h later to inquire about any adverse events and reminded to contact study personnel if any adverse events were to occur. Muscle biopsies are performed at two timepoints, the first one at least a week before the first exercise session and the second 5 days after the last exercise session.

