### Outcome measures

#### OGTT

Outcome measures are determined as previously described [32]. Briefly, plasma glucose is measured at 0, 1 and 2 h using a glucose Analox analyzer (GM7 Analox microstat, Analox Instruments, USA) and area under the curve calculated. Plasma insulin and C-peptide are measured at 0, 1 and 2 h using ELISAs (Millipore Human Insulin ELISA, cat.no. EZHI-14 K; Alpco C-Peptide ELISA, cat.no. 80-CPTHU-E10.1). HOMA-IR is calculated (fasting glucose (mg/dL) x fasting insulin (µU/mL) divided by 405) and HOMA-β is calculated as 60 × fasting insulin (μU/mL) / (fasting glucose (mg/dL)—63). High molecular weight adiponectin is measured in the baseline samples using an ELISA (Alpco HMW Adiponectin ELISA, cat.no. 80-ADPHU-E01).

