### Data management and analysis

All data are entered into REDCap and are handled with confidentiality. Personal information of participants such as phone number and email addresses are used only to contact the participant. Names of participants appear only in the demographic form. The participants’ demographic and outcome measures of interest pre- and post-exercise intervention will be summarized using descriptive statistics. Mean, standard deviation, and range will be calculated for continuous variables, and frequencies and percentages will be generated for categorical variables. For continuous variables (such as VO_2max_, OCR, ECAR), the normal distribution assumptions will be tested. If necessary, the data will be transformed to follow the normal distribution assumption. If the normality assumption cannot be met, these variables will be classified as categorical or analyzed using non-parametric tests. For categorical variables (e.g., glucose at 2 h, HOMA-IR, HOMA-b) clinical cutoff values will also be used. The changes in the outcome measures (e.g., OGTT outcomes, bioenergetic measures, microRNA expression, RHR, VO_2max_, MOCA measures, ASA24 measures) between pre and post exercise intervention will be tested using the paired t-test. Linear regression models will also be used to analyze the relationship between alcohol use with the outcome measure changes as the dependent variable, adjusting for potential confounding factors (such as age, sex, race, viral load and CD4 counts). If there is matching or balance achieved, age and gender will be used as categorical variables rather than confounders. A p < 0.05 will be used for statistical significance.

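### An uncontrolled pre-post comparison after entry on one finger-stick glucose cannot show the exercise effect that the article promises, and the limitations do not say so

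*Protocol article*

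**What the plan says.** - **Entry.** The Screening section of the protocol article states: "Participants are considered eligible if they have a fasting blood glucose of 95–124 mg/dL", "measured by a single-use auto-disabling finger stick device and glucose meter". No repeat reading is described. The abstract gives a slightly different window ("Participants who have a fasting blood glucose level between 94 and 125 mg/dl will be enrolled in the study") and Table 1 gives 94–124 mg/dL. The three need reconciling, but the argument here does not depend on which is used.
- **Baseline for analysis.** This is not the screening reading. Under Oral glucose tolerance test (OGTT), "Blood is collected at time 0, after which participants ingest a calibrated dose". Under Outcome measures, "plasma glucose is measured at 0, 1 and 2 h using a glucose Analox analyzer". HOMA-IR and HOMA-β are calculated from fasting glucose and insulin.
- **Main test.** Under Data management and analysis, changes in outcome measures "between pre and post exercise intervention will be tested using the paired t-test", at p < 0.05. Regressions of change on alcohol use are also planned, and a dose-response analysis where sessions are missed.
- **Claim.** The abstract says: "Results generated will demonstrate the effect of exercise on glycemic measures in PLWH with subclinical dysglycemia and at-risk alcohol use". The Discussion makes a similar claim about determining the impact of the intervention.
- **Limitations.** The section discusses resistance exercise, diet monitoring and a behavioural add-on. It mentions neither a comparison group nor regression to the mean.
- **A further fasting sample.** Participants fast for 9 h before the biopsy visit. "Following the 0 h blood collection, participants consume a defined (calorie and nutrient composition) meal". No glucose or insulin assay on that blood is described.

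**The concern.** In a single exercised group, the pre-post difference contains everything that happened over the interval: exercise, drift over time, familiarity with testing, and changes in diet or drinking. The article itself expects that diet and alcohol use might change and plans to look at both. The paired test cannot divide the change among these causes, yet the stated conclusion gives it to exercise.

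Entry on a raised reading may add a further component. People chosen because one fasting value lies in an upper window tend to read lower next time without treatment. If that component enters the baseline, fasting glucose and the two HOMA indices can appear to improve with no exercise effect. These measures belong to the glucose-insulin family that the abstract names within the primary outcome.

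**Working it through.** The article gives no SD, effect size or sample size calculation, so there is no stated figure to reproduce. The check has two parts.

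**1. Can any planned comparison isolate exercise?**
- Paired t-test: exercised participants before and after, with no unexposed group.
- Regression of change on alcohol use: exercised participants with more against less alcohol use.
- Dose-response by sessions attended: exercised participants with more against fewer sessions, where attendance is not assigned.

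None supplies an unexposed comparison.

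**2. How large could regression to the mean be?**

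Model with no exercise effect: a person's true fasting glucose is normal with mean μ and SD b. Each day adds a deviation with SD w. The screening meter adds error with SD m, and the laboratory analyser adds error with SD 1.5. Selection is 95 ≤ screening reading ≤ 124.

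*From the article:* the window; 33 completers as of November 2022; 155 of 242 consented met eligibility, 155/242 = 64%.

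*Assumed, not in the article:* μ = 85 to 105 mg/dL; (b, w, m) = (8, 4, 3), (10, 6, 5) or (12, 8, 6); two-sided 0.05 test.

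Let S² = b² + w² + m², α = (95 − μ)/S and β = (124 − μ)/S, with φ and Φ the standard normal density and distribution function. Then:
- share passing = Φ(β) − Φ(α)
- mean excess of the selected readings over μ: E = S·[φ(α) − φ(β)] / share passing
- null fall if the OGTT is on the screening day = (w²/S²)·E. Only the shared day's deviation carries over; the meter error does not, because the baseline is a separate laboratory measurement.
- null fall if the OGTT is on another day = 0

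Worked case, μ = 100 and SDs (10, 6, 5): S² = 100 + 36 + 25 = 161, S = 12.69, α = −0.394, β = 1.891. Share passing is 0.624. E = 6.15. The same-day null fall is (36/161) × 6.15 = 1.4 mg/dL. The SD of the paired difference is about 8.4, so the noncentrality is 1.375 × √33 / 8.43 = 0.94. The chance of a significant improvement is then 14.7%.

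Settings whose pass rate (56–72%) is near the article's 64%, OGTT on the screening day, n = 33:

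| μ | b, w, m | Share passing | Null fall (mg/dL) | Chance of false improvement |
|---|---|---|---|---|
| 100 | 8, 4, 3 | 70% | 0.8 | 12% |
| 100 | 10, 6, 5 | 62% | 1.4 | 15% |
| 100 | 12, 8, 6 | 56% | 1.9 | 16% |
| 105 | 10, 6, 5 | 72% | 0.6 | 6% |
| 105 | 12, 8, 6 | 63% | 0.9 | 7% |

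The nominal rate in the direction of improvement is 2.5%. Simulation agrees with these values to within about one percentage point.

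Over the whole assumed grid, the same-day null fall is 0.4–4.9 mg/dL and the false-improvement rate 5–73%. The large values need μ well below 100, where at most half of those screened would pass, which fits the 64% poorly. With the OGTT on another day, simulation gives 0.0 mg/dL and about 2.5% throughout.

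**The case against.** The strongest reply is that the analysed baseline is not the value used for selection. It is a separate plasma sample on a laboratory analyser, and if drawn on another day its expected selection bias is zero. This stands. A reader might infer that regression to the mean will necessarily be counted as an exercise benefit, or that the screening meter reading serves as the baseline. The article supports neither.

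Whether the two share a day cannot be settled from the text. Two features point towards a shared visit: the only overnight-fast instruction before the OGTT is the screening one, and 152 of the 155 eligible (98%) had the OGTT. Three eligible people without an OGTT is equally compatible with separate visits. The timeline is in a figure that is not available here, so its absence is no fault of the plan.

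Three further replies also stand:
- The 64% is only a rough guide to truncation, because prescreening and other entry criteria affect it. If some people failed on other criteria, more than 64% passed the glucose window and the bias would tend to be smaller.
- Regression to the mean acts on fasting glucose and the HOMA indices. It reaches 2-h glucose only through correlation, and fitness and myoblast measures hardly at all.
- The article is condensed, so silence about assays on the biopsy-visit blood does not prove that none is done.

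None of these replies answers the point about the claim. The abstract's conclusion and the list of limitations are the article's own text, not detail left to a fuller plan.

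**Conclusion.** The point holds for the conclusion the article promises. A paired pre-post test in one exercised group estimates change. It does not identify how much of that change exercise caused, and the limitations do not say so. This applies to every outcome and does not depend on regression to the mean.

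Regression to the mean is a possible addition for fasting glucose, HOMA-IR and HOMA-β. For fasting glucose, if the baseline OGTT is on the screening day, its size is about 0.6–1.9 mg/dL, with a 6–16% chance of a false significant improvement against 2.5%. If it is on another day, the bias is about zero. The range rests on assumed SDs and source means, on a pass rate near 64%, and on 33 pairs, which is an interim count in a study still under way.

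**What to change.** 1. Reword the abstract's conclusion, and the matching sentence in the Discussion, so that the study estimates the pre-post change in glycemic measures rather than demonstrating what exercise causes.
2. Add the lack of an unexposed comparison to the limitations, naming time trends, diet and alcohol changes, and regression to the mean for the fasting measures.
3. State in the text whether the baseline OGTT is on the screening day.
4. Measure glucose and insulin in the 0 h blood from the pre-intervention biopsy visit, if this is not already done. Among participants with both samples, report the untreated OGTT-to-biopsy change beside the pre-post change.
5. If screening and OGTT share a day, use the biopsy-visit value as a sensitivity baseline. Do not average it with the OGTT value: averaging keeps half of any same-day bias. Averaging at the post-intervention visits would also mix samples taken 3 and 5 days after the last session.

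The cost is a small number of assays on blood already drawn, some wording, and a more modest claim. Step 4 measures short-term untreated change only; it does not replace a comparison group over the 10 weeks.

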**Conclusions:**

The proposed intervention will also have the potential to be scalable to promote lifestyle changes among PLWH, particularly in underserved communities.

## Background

With effective antiretroviral therapy (ART), people living with HIV (PLWH) have near normal life expectancy and increased risk of age-associated comorbidities. Cardiometabolic comorbidities [1–6], are among the leading causes of morbidity and mortality among PLWH [1–5, 7, 8]. At-risk alcohol use is more frequent among PLWH than the general population and increases the risk of health challenges [9–11]. Our multidisciplinary research team is conducting a longitudinal clinical observational study, the New Orleans Alcohol and HIV study (NOAH) [12], to examine the impact of at-risk alcohol use on risk for comorbidities in PLWH. The study population is comprised of majority socioeconomically disadvantaged and majority Black/African American individuals in the Greater New Orleans Area. Data indicate that 57% have at-risk alcohol use [12], ~ 36% meet criteria for metabolic syndrome, ~ 50% have insulin resistance as measured by the Homeostatic Model Assessment of Insulin Resistance (HOMA-IR), and ~ 15% meet criteria for type 2 diabetes[13]. Results also showed a significant negative association between HOMA-β, a surrogate indicator of pancreatic cell function, and multiple measures of alcohol use including Alcohol Use Disorders Identification Test (AUDIT)-C, 30-d Timeline Followback (TLFB), and a biomarker of recent alcohol use Phosphatidylethanol (PEth) [13].

Previously, studies in simian immunodeficiency virus (SIV)-infected macaques, a preclinical model of HIV, showed that chronic binge alcohol (CBA) significantly impaired endocrine pancreatic response to a glucose load [14], and increased pathophysiological alterations in multiple metabolically active organs [15]. CBA administration also increased skeletal muscle proteasomal activity, impaired anabolic pathways and insulin signaling [16–19] and altered mitochondrial bioenergetic function [20, 21]. Together, these findings suggest that at-risk alcohol use increases risk of metabolic dysregulation in PLWH, and in a preclinical model of HIV infection, highlighting the importance of developing interventions to ameliorate disease burden. Specifically, strategies to reduce cardiometabolic comorbidities and improve overall quality of life that can be scalable and can be implemented in clinical and community settings are urgently required to mitigate health disparities.

Evidence suggests that people engaging in regular aerobic exercise preserve or improve glycemic control, cardiovascular function, skeletal muscle function, have reduced risk of metabolic syndrome, and improved quality of life [22, 23]. Specifically, structured walking for approximately 30 min three times per week reduces fasting glucose, hemoglobin A1c, and HOMA-IR [24, 25]. Moreover, PLWH engaging in exercise have increased energy, improved self-concept, increased physical fitness, mental health, improved cardiometabolic measures, body composition and immune function [23, 26–30]. Studies show that moderate intensity exercise (40–60% heart rate reserve [HRR]) improves mitochondrial dysfunction, insulin resistance and diabetes among PLWH [31]. Additionally, our studies in the preclinical SIV model provided evidence that ex vivo β2 adrenergic stimulation of muscle myoblasts improved mitochondrial bioenergetics and mitochondrial copy number [21] supporting the hypothesis that aerobic exercise may improve mitochondrial homeostatic mechanisms resulting in improved glycemic control. Despite compelling evidence that exercise can be an effective strategy to improve metabolic health, little is known of how exercise improves metabolic health in PLWH, particularly those with at-risk alcohol use.

Based on our preclinical and clinical observational studies and evidence from the literature, we launched the Alcohol & Metabolic Comorbidities in PLWH: Evidence Driven Interventions Study (ALIVE-Ex Study, NCT03299205). This is an ongoing longitudinal prospective, interventional study investigating the effects of aerobic exercise in PLWH with fasting dysglycemia and at-risk alcohol use. The study consists of two phases. The objective of the first phase was to determine whether PLWH with at-risk alcohol use had increased risk of dysglycemia and dysregulated muscle metabolic function. The overall objective of the second phase of the study is to determine whether moderate intensity aerobic exercise will improve measures of whole-body glucose insulin dynamics and improve skeletal muscle metabolic and bioenergetic function. The secondary objective of Phase 2 is to determine whether the exercise intervention improves cognitive function and overall quality of life.

## Methods

### Study overview

The ALIVE-Ex study is an aerobic exercise intervention (NCT03299205) conducted among PLWH in the Greater New Orleans Area. The study was approved by the Institutional Review Board of Louisiana State University Health Sciences Center-New Orleans (LSUHSC-NO # 736) was launched in 2017 and is expected to continue through 2023.

### Study setting

Initially, ALIVE-Ex leveraged participants from the NOAH study. NOAH participants are a clinic-based sample of PLWH aged ≥ 18 years under care at the HIV outpatient clinic of the University Medical Center-New Orleans (UMC-NO) [12]. In 2018, the ALIVE-Ex study expanded recruitment beyond NOAH to the community of the Greater New Orleans area.

### Recruitment

Potential participants were invited to voluntarily join the study. Study enrollment started in November 2017 and is anticipated to stop in May 2023. Based on the eligibility criteria, letters were sent to NOAH participants inviting them to the study. Other recruitment efforts included posting study flyers in local pharmacies, HIV clinics, local HIV Community Advisory Boards, and relevant community events. Past and ongoing recruitment efforts also include invitations during clinic visits, advertisements, use of social media, health care provider referrals, and presenting the study at local HIV community advisory boards.

### Consent

Study purpose, details, risks, and benefits are thoroughly explained to participants and any questions answered. Participants must verbally demonstrate understanding and provide written informed consent before inclusion in the study. Participants receive compensation for all testing procedures and exercise sessions.

### Study timeline

The study timeline is as shown in Fig. 1. The eligibility criteria are shown in Table 1.

**Fig. 1 Fig1:**
[figure not shown]
Study timeline for the Alive-Ex research protocol

**Table 1 Tab1:** Inclusion and exclusion criteria for the ALIVE-Ex Study

Inclusion criteria	Exclusion criteria
PLWH ≥ 18 years of age	Diagnosed diabetes (self-reported)
Fasting plasma glucose between 94 and 124 mg/dl	Lack of informed consent
Answered “No” to all questions of PAR-Q, with the exception that if participants answered “yes” to taking medications for high blood pressure, they were evaluated at medical clearance and enrolled into the study, based on the discretion of the cardiologist	Non-English speaking
	Females who are pregnant
	Acute alcohol intoxication on any visit days as determined by breathalyzer
	Additional exclusion criteria for exercise intervention
	Orthopedic or cardiovascular complications that preclude from exercise
	Peripheral neuropathies
	Allergy to lidocaine
	Use of anticoagulant medication (blood thinners)
	Acute illness within the preceding six weeks of study visit (fever, new antibiotic use, or unscheduled healthcare visit (for illness)

### Screening

After informed consent, participants are instructed to fast and not drink alcohol overnight. Participants are considered eligible if they have a fasting blood glucose of 95–124 mg/dL, measured by a single-use auto-disabling finger stick device and glucose meter (True Metrix® Pro Blood Glucose Monitoring System, McKesson).

### Oral glucose tolerance test (OGTT)

Blood is collected at time 0, after which participants ingest a calibrated dose (10 oz) of a glucose solution (Trutol; 75 g glucose) over a 5-to-15-min period. Blood is collected at 1 and 2 h following the glucose drink. During that time, participants are seated without eating, drinking, or smoking and complete the following questionnaires: demographics, AUDIT, and TLFB. At the end of the OGTT, participants are monitored for signs of hypoglycemia. OGTTs are performed at two timepoints, the first one at least a week before the first exercise session and the second 3 days after the last exercise session.

### Medical clearance

A cardiologist affiliated to LSUHSC-NO provides medical clearance for eligibility for exercise intervention. Approval for subject participation in the exercise protocol is based on absence of significant cardiovascular impairments (i.e., angina, clinically significant arrhythmias, uncontrolled hypertension); absence of significant peripheral neuropathies or conditions that would increase risk of falls or limit ability to safely exercise on a treadmill; and absence of active cocaine or amphetamine use. The resting heart rate (RHR) recorded during the electrocardiogram (ECG) is retained and used for HRR calculation.

